### Study Design and Setting

Both AI-INFOCARE and AI-MEDTALK are designed as prospective, parallel-group RCTs. The trials share a common overall design, with nearly identical interventions and outcomes, but target different patient populations and phases of care (outpatient pretreatment vs inpatient discharge). The study setting is the Department of Neurosurgery at University Hospital Carl Gustav Carus, Technische Universität Dresden, Germany, which includes outpatient clinics and inpatient wards. The trials are investigator-initiated collaborations between the hospital and Simply Onno GmbH (Berlin; [9]), a health AI startup.

The overall structure of the trials is summarized in Figure 1. Each trial will enroll participants over a 6-month recruitment period and follow a simple two-arm randomized design (intervention vs control). There is no blinding (open-label) and no crossover between arms. Outcome assessments are conducted at a single postintervention time point (immediately after the index doctor–patient consultation during which the intervention could have an effect). There are no long-term follow-ups in this protocol, as the primary focus is on the immediate communication outcomes of the consultation.

**Figure 1 figure1:**
[figure not shown]
Flow diagram of the trial design for AI-INFOCARE and AI-MEDTALK. Both trials follow the same procedure: eligible patients are approached and consented, then randomized 1:1 to receive either the artificial intelligence (AI)–generated layperson summary of their medical document (intervention) or standard care with no summary (control) before their doctor consultation. The consultation proceeds as usual, and afterward outcomes are assessed through questionnaires and data collection. Finally, data will be analyzed comparing the two groups.

### Participants and Recruitment

Each trial will recruit approximately 300 patients (150 per arm), for a total of 600 participants across both trials. Participants will be recruited consecutively from the patient population served by the neurosurgery clinic. AI-INFOCARE will enroll ambulatory patients before a planned treatment, and AI-MEDTALK will enroll hospitalized patients at discharge after surgery.

#### AI-INFOCARE (Outpatient Cohort)

Eligible patients are adults scheduled for a neurosurgery outpatient appointment in preparation for a procedure or treatment discussion. Examples include patients referred for elective neurosurgical procedures (e.g. tumor resection, spine surgery) who have prior medical reports (such as referral letters, imaging reports) that will be discussed during their consult. Enrollment will occur when the patient arrives for their pretreatment consultation or is identified shortly beforehand via appointment lists.

#### AI-MEDTALK (Inpatient Cohort)

Eligible patients are adults who have undergone a neurosurgical operation and are now being discharged from the hospital. Typically, such patients receive a discharge summary document and a briefing from the surgical team about the operation findings, postoperative care, and follow-up. Enrollment will occur on the day of discharge, prior to the discharge consultation.

#### Inclusion Criteria (Both Trials)

Eligible participants are adults aged 18 years or older and capable of providing informed consent, with sufficient German language proficiency to read the documents and complete questionnaires (the intervention and all outcome measures are in German). For AI-INFOCARE, the patient must have at least one relevant medical document available, such as a referral letter or diagnostic findings, that can be provided to them. For AI-MEDTALK, a written discharge summary or report must be prepared as per standard care, which can be used for the intervention. Participants must be willing to take part in the study and able to complete a brief survey after the consultation.

#### Exclusion Criteria (Both Trials)

Exclusion criteria include patients with severe cognitive impairment, altered mental status, or diagnosed dementia or delirium that would prevent comprehension of materials or completion of surveys. Patients who are unable to read (due to illiteracy or severe visual impairment that cannot be corrected) or unable to communicate in German are also excluded. Patients in emergency situations or acute distress where the study procedures could interfere with urgent care, such as an acute postoperative complication requiring intensive care, are not eligible. Inpatients who have had an extremely prolonged hospital stay with multiple prior discussions, which might dilute the effect of a one-time summary at discharge, are excluded. Any patient whom the treating physician deems inappropriate for the study—for example, due to extreme anxiety or other psychosocial factors, defined as inability to complete consent or questionnaires despite support or requiring acute intervention documented by staff—is also excluded. Finally, participation in another interventional study that could conflict with outcomes, or prior enrollment in the current trials (to avoid duplicate participation if a patient were first an outpatient and later an inpatient) renders a patient ineligible; in such cases, they would only be enrolled in one of the two trials.

#### Screening and Recruitment

A study team member (a trained research nurse or physician) will screen upcoming clinic appointments and inpatient lists daily to identify potential participants meeting the above criteria. Recruitment is consecutive, meaning every patient who meets criteria is approached without selection beyond eligibility, to minimize sampling bias. Patients will be provided written and oral information about the study, and written informed consent will be obtained by study personnel prior to randomization. The general nature of the intervention (receiving an AI-prepared explanation) will be explained, but participants will not be explicitly told whether their documents have been simplified by AI until after the consultation (to avoid expectation bias, although patients in the control arm will likely notice the absence of a simplified text). They are told that the study is comparing different ways of providing information.

At the time of consent, baseline data will be collected, including demographics (age, sex, education level) and clinical context (diagnosis, type of document available). No identifiable personal health data beyond what is needed for outcomes will be retained in the research dataset, and all AI processing of documents occurs on secure servers in adherence with privacy regulations (no patient-identifying information is input to the AI model). Participants are free to withdraw at any time. We anticipate high acceptability of the intervention; similar studies have reported that patients appreciate receiving additional explanations [7].

### Randomization and Blinding

Randomization was performed using a computer-generated randomization list created prior to study start. The list was produced with a validated random number generator, fully covering the planned sample size for each trial (n=300). Assignments were generated in a 1:1 ratio (intervention vs control) and exported into a password-protected file with time-stamp documentation. The randomization list was stored on a secure hospital server, accessible only to the principal investigator and the designated study statistician. Allocation concealment was maintained because recruiting staff and treating physicians had no access to the sequence; group assignment for each newly enrolled participant was revealed sequentially through a locked module at the point of inclusion. This procedure prevents prediction of future allocations while ensuring reproducibility and auditability.

Due to the nature of the intervention, blinding is not possible for participants or treating physicians. Patients in the intervention arm will receive an additional written summary that is clearly different from standard documents, and physicians will likely recognize if a patient has an easy-summary or not (eg, patients might refer to it during the consult). We considered having a blinded outcome assessor, but our outcomes are primarily self-reported by patients and the treating physician immediately after their encounter, so blinding is not applicable. The study analysts will remain blind to group labels until after data analysis (groups will be coded as A and B during statistical analysis to prevent subconscious bias). While lack of blinding may introduce some risk of bias, outcomes such as questionnaire scores are less prone to observer bias and more a reflection of the participant’s genuine experience. We will compare certain objective measures (like consultation length) to see if any Hawthorne effect (change in behavior due to being studied) is present similarly in both groups.

To mitigate expectancy and performance bias, we use several safeguards: (1) all participants receive a standardized neutral script at enrollment (“You will receive information materials that may vary in format”); (2) clinicians are instructed not to explicitly reference the AI summaries; (3) objective endpoints, such as consultation time, complement self-reported measures; (4) the analyst is blinded to group codes; and (5) sensitivity analyses adjusted for age, education, and clinician identifier will be conducted.

### Intervention: AI-Generated Layperson Summary

#### Intervention (AI-Based Translation)

Participants randomized to the intervention will receive a layperson-friendly summary of their medical documents, generated by an AI language model, in addition to the standard care documents. Specifically, for each patient, we will take the relevant medical text (eg, referral letter from the general practitioner detailing the condition and prior investigations, or the hospital discharge summary, which includes diagnosis, procedures, and follow-up recommendations) and process it through an AI system that produces an easy-to-understand version in German. The AI system, provided by Simply Onno GmbH, is built on the Claude 3.5 LLM (Anthropic), which has been configured through prompt engineering for patient-facing simplification. The model was instructed to rewrite the input document in clear, simple language targeting approximately a B1 reading level (roughly middle school reading ease). It replaces medical jargon with everyday terms (or explains them), expands abbreviations, and structures the information into a patient-oriented format (for example, using short bullet points or headings for diagnosis, treatment, and next steps).

Before being given to the patient, each AI-generated summary undergoes a quick verification by a member of the study team (typically a physician or medically trained researcher) to catch any obvious errors or unsafe omissions. This step is essential because LLMs can occasionally produce inaccuracies (“hallucinations”); any such instance will be corrected by the reviewer. In practice, the review has shown the summaries to be accurate, with occasional need to adjust a phrase. The final approved summary, typically 1-2 pages in length, is then provided to the patient before their consultation with the doctor.

To ensure fidelity, reviewers follow a 12-item checklist covering accuracy of diagnoses and procedures, completeness of follow-up instructions, preservation of risk or urgency language, and absence of contradictions or invented content. Ten percent of summaries undergo dual review, with interrater agreement reported (Cohen κ and intraclass correlation coefficient). A predefined correction log template (Multimedia Appendix 1) will be used to categorize and document any issues detected during validation. As the trial has not yet commenced, no entries are available at this stage.

For copyright and intellectual property reasons, the exact prompts cannot be disclosed. However, all prompts were version-controlled, and each version was archived with time-stamps in the study’s secure documentation system. Any changes in prompt wording or model parameters were logged and linked to the summaries generated during that phase. This ensures transparency and reproducibility of the process without requiring disclosure of proprietary content.

For outpatients (AI-INFOCARE), the summary is handed to them at the clinic check-in, so they can read it while waiting. For inpatients (AI-MEDTALK), the summary is given on the morning of discharge, a few hours before the formal discharge meeting with the physician. Patients are encouraged to read the summary and note any questions they have. They are told that this is “an explanation of your medical letter in simple language that you can keep.”

The physician conducting the consultation is aware that the patient has this summary (and in many cases, the physician will have seen it, since it mirrors the content of their own letter but in simpler form). However, physicians are instructed to conduct the consultation as they normally would, with no special training or script from the study. They will naturally address patient questions or clarify misunderstandings as needed. We will later examine whether having the summary changed the nature of questions patients ask or the flow of conversation (captured indirectly through outcomes such as consultation length and perception measures).

#### Control (Usual Care)

Participants randomized to the control arm go through usual care procedures without any additional intervention. For outpatients, this means they have whatever documents they normally would (often patients do bring their referral letter or test results, but these are in technical language, and we do not provide any translated version). They will have their consultation with the doctor using those standard materials. For inpatients, usual care means they receive the standard discharge summary at the end of the discharge discussion (or sometimes given to them to hand to their next doctor), but not ahead of time in simplified form. Essentially, the control group represents the status quo: the patient relies on the doctor’s oral explanation during the consultation and on the standard medical documents, with no separate plain-language text.

All other aspects of care are identical between groups. Both groups’ consultations take place with the same pool of physicians (neurosurgery attendings or senior residents), in the same settings. Physicians will have the original medical documents in both cases for reference. After the consultation, both groups complete the outcome questionnaires described below.

Notably, if a patient in the control group expresses strong confusion about their medical documents or requests an explanation in writing, the physician will handle it per usual care (which might involve some oral explanation or writing brief notes, but the prepared AI summary will not be provided at that point, to preserve the integrity of the comparison). However, at the end of the study, control patients will be offered the layperson-friendly summary if they desire, as an ethical consideration to avoid denying potentially helpful information.

### Outcome Measures

#### Overview

We chose outcome measures that capture multiple dimensions of doctor–patient communication and the effects of improved information comprehension. The outcomes have been validated in prior research and will be assessed for each patient (and their physician, in one measure) immediately after the consultation. Figure 2 outlines and illustrates the relationship between the outcomes and instruments, categorized as patient-reported, physician-reported, and objective measures. The specific outcome measures are described in the following sections.

**Figure 2 figure2:**
[figure not shown]
Outcome structure for communication evaluation. The trials assess patient-reported outcomes (communication quality and autonomy support through the Fragebogen zur Arzt-Patient-Interaktion [FAPI] and brief Health Care Climate Questionnaire [HCCQ], and the patient’s self-rated understanding), a physician-reported outcome (encounter difficulty through the Difficult Doctor–Patient Relationship Questionnaire [DDPRQ-10]), and an objective measure (consultation duration).

#### Primary Outcome

We designate the patient’s perceived quality of the doctor–patient interaction as the primary outcome, measured by the FAPI (known in English as the Questionnaire on the Quality of Physician–Patient Interaction [QQPPI]). The FAPI is a 14-item self-report questionnaire developed and validated in Germany to gauge the quality of a specific medical consultation from the patient’s perspective. It covers aspects such as the doctor’s empathy, clarity of explanations, patient involvement in decisions, and time given. Each item is a statement (eg, “The doctor explained the treatment options in an understandable way” or “I felt the doctor took my concerns seriously”) rated on a 5-point Likert scale (“not at all” to “very much”). An overall FAPI score is calculated as the mean of item scores (after appropriate reversal of any negatively worded items), with higher score indicating better interaction quality. The FAPI has demonstrated excellent psychometric properties in previous studies, with Cronbach α around 0.95-0.97, indicating high internal consistency. It has shown convergent validity by correlating strongly with patient satisfaction and decision comfort. In these trials, the FAPI is administered in German immediately after consultation. We hypothesize that FAPI scores will be higher in the intervention group, reflecting an improved communication experience when patients have had the opportunity to understand their medical information beforehand.

#### Secondary Outcome 1: Perceived Autonomy Support From the Physician

This outcome is measured by the HCCQ. The HCCQ is a widely used instrument rooted in self-determination theory, assessing the degree to which the patient feels their doctor was autonomy-supportive versus controlling [10]. We will use the 6-item brief HCCQ (German version), with items like “My doctor encouraged me to ask questions” and “I felt understood by my physician,” rated on a 7-point Likert scale [10]. Scores are averaged, with higher scores indicating more autonomy support. The HCCQ has been validated in multiple contexts, showing strong reliability (Cronbach α approximately 0.90) [11]. This outcome captures an important facet of communication quality—whether having more knowledge through the summary makes patients feel more respected and involved in the conversation. We anticipate higher autonomy support in the intervention arm, as doctors may not need to adopt a directive stance and patients may participate more actively when they understand the information.

#### Secondary Outcome 2: Patient’s Self-Rated Understanding of the Information Discussed

This is a single-item outcome where, after the consultation, we ask the patient: “How well do you feel you understood the information and explanations given to you during this consultation?” on a 5-point Likert scale (1=not at all, 5=very well). This simple metric is commonly used in communication studies and correlates with knowledge retention. It serves as a direct subjective indicator of whether the intervention fulfilled its immediate purpose (improving understanding). We will compare the distribution of responses between groups, expecting a higher proportion of “well” or “very well” responses in the AI summary group. Even a one-point improvement on this scale would be meaningful in practice.

#### Secondary Outcome 3: Physician’s Perception of the Encounter Difficulty

This outcome is measured by the Difficult Doctor–Patient Relationship Questionnaire, 10-item (DDPRQ-10) version [12]. The DDPRQ is a survey the doctor fills out after seeing a patient, reflecting how “difficult” or frustrating the physician found the encounter. It touches on feelings like “I found this patient difficult” or “This was a frustrating visit,” rated typically on a 6-point scale [13]. We are using the 10-item short form (each item 1=not at all, 6=a lot), which has been shown to retain high reliability (Cronbach α approximately 0.93) [12]. A total score is averaged (higher score means the doctor perceived the patient as more difficult). We chose this outcome to capture the physician’s side of the communication dynamic. Often, patients who are confused, anxious, or demanding due to lack of understanding can be perceived as “difficult” by doctors [13]. We hypothesize that doctors will rate encounters in the intervention arm as less difficult on average, since patients may be more at ease and focused on pertinent questions rather than expressing confusion or dissatisfaction. Each patient’s consulting physician will complete the DDPRQ-10 immediately after the consultation, before seeing the next patient, to ensure responses reflect that specific encounter.

#### Secondary Outcome 4: Consultation Duration

We will record the length of the consultation (in minutes) from start to finish. In the outpatient setting, a research assistant will unobtrusively note the time the patient enters and leaves the doctor’s office. In the inpatient discharge setting, the time of the conversation with the doctor (often in the patient’s room or ward office) will be noted. This outcome addresses efficiency, as providing patients the summary could either increase time if patients ask more questions or discussion goes deeper, or decrease time if basic explanations need less repetition. Previous research offers mixed insights—sometimes better-informed patients make visits slightly longer due to more questions, but those questions may be more to the point, and satisfaction improves. We do not consider a modest change in time inherently negative; however, it is important to document if the intervention significantly alters physician time burdens. Our expectation is that consultation time might not differ greatly or could even decrease in the intervention group if clarification of basics is faster. This outcome is measured in a single-blind fashion, with the person timing is not influencing the interaction.

In addition to these main outcomes, we will collect exploratory data, for instance the number of questions patients ask during the consultation (not formally tallied, but physicians will provide a subjective rating of patient engagement) and any specific misunderstandings noted (physicians can report if they had to correct any wrong notions the patient had from reading the summary or otherwise). We will also debrief patients in the intervention group with a couple of questions about the summary itself (eg, “Did you find the AI-generated explanation helpful?” rated yes or no, and an open comment). These will be reported qualitatively to supplement interpretation, but they are not primary outcomes.

### Sample Size and Power Calculation

We determined the target sample size of 300 patients per trial (150 per arm) through power analysis based on the primary outcome (FAPI score). From previous studies using the FAPI/QQPPI in similar settings, we estimate the mean (SD) FAPI score in usual care to be approximately 3.5 (SD 1.0) on the 5-point scale. We consider an increase of 0.3-0.5 in the mean score (with 0.5 being a medium effect, roughly half an SD) to be a clinically important improvement in communication quality. To detect a difference of 0.5 with 80% power at a 2-sided α of 0.05 using a 2-sample *t* test (2-tailed), approximately 63 patients per group are required. To be conservative and account for potential dropout or non-evaluable responses (eg, incomplete questionnaires), we inflated the sample. Our goal of 300 participants per trial (150 per arm) provides >90% power to detect an effect size of *d*=0.5 and approximately 80% power to detect a smaller effect of *d*≈0.4. This sample also provides ample power (>80%) for detecting differences in secondary outcomes, such as a 10-point difference in the 0-100 scaled DDPRQ-10 or approximately a 1-point difference in the understanding rating. We do not plan an interim efficacy analysis, but an internal check of assumptions, such as variance, will be conducted after approximately 50% enrollment to ensure the sample size remains adequate. Given the consecutive recruitment strategy, we anticipate reaching 300 patients in each trial within the planned 6-month recruitment window, as the neurosurgery service sees dozens of new patients weekly and discharges dozens monthly, with a good proportion expected to consent.

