**Results:**

Each trial targets 300 participants (150 per arm), providing greater than 80% power for an effect size *d*≈0.4 on the primary outcome (α=0.05). Outcomes are assessed immediately after the index consultation, with no additional follow-up planned in this protocol. We hypothesize that providing layperson-friendly summaries will significantly improve patients’ understanding and satisfaction with information, foster a more autonomy-supportive communication climate, and reduce physicians’ perceived difficulty in the encounter without unduly prolonging consultation time. Neither study received external funding. Both trials are currently in the recruitment phase, with patient enrollment scheduled to begin in May 2025 and expected to conclude by February 2026. Results are anticipated to be published in summer 2026.

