### Statistical Analysis Plan

We will first describe the sample using summary statistics (means or medians for continuous variables, frequencies for categorical variables). The two trial populations (outpatient vs inpatient) will be described separately. Baseline characteristics will be compared between arms to ensure that randomization achieved balance; any significant differences will be noted and adjusted for in secondary analyses if needed.

For the primary outcome (FAPI score), we will compare the intervention and control group means using an independent-samples *t* test (or nonparametric Wilcoxon rank-sum test if the distribution is highly skewed, although previous studies suggest near-normal distribution). We will report the mean difference with 95% CI. The primary analysis will be carried out separately for each trial. However, since the interventions and outcomes are identical, we may also perform a pooled analysis across both trials to increase power, including an indicator for trial to account for any systematic differences in context. Our hypothesis test is 2-sided with α=0.05. We anticipate a positive difference (intervention > control).

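### The sample-size section understates power at d≈0.4: on its own inputs 150 per arm gives about 93%, not about 80%

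*Protocol article*

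**What the plan says.** The Sample Size and Power Calculation section of the protocol article sets these terms for each trial:

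- Variability: "we estimate the mean (SD) FAPI score in usual care to be approximately 3.5 (SD 1.0) on the 5-point scale".
- Important difference: "We consider an increase of 0.3-0.5 in the mean score", that is, 0.3 to 0.5 SD at the assumed SD.
- Base calculation for a difference of 0.5, "with 80% power at a 2-sided α of 0.05 using a 2-sample" t test: "approximately 63 patients per group are required".
- Target: 150 per arm, reached by an inflation for dropout and unusable questionnaires with no rate given. At half an SD, the section puts the power of this target above 90%.
- For the next smaller standardized effect, about 0.4, the same target is credited with "approximately 80% power to detect a smaller effect of" that size.

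The Results paragraph of the abstract describes the same target as "providing greater than 80% power for an effect size" of d≈0.4. The Statistical Analysis Plan section confirms the error rate ("Our hypothesis test is 2-sided with α=0.05"), the independent-samples t test and a separate primary analysis in each trial. No power is given for a difference of 0.3.

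**The concern.** The base calculation and the claim at d≈0.4 do not fit together. Sample size for a t test scales with 1/d². If about 63 per group give 80% power at 0.5, then 80% power at 0.4 needs about 63 × (0.5/0.4)² = 98 per group. The plan has 150, so power at 0.4 must be well above 80%.

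What is at stake is the accuracy of the power statement for the primary outcome. A reader cannot tell from it which effect the trial can detect with 80% power. The section also calls 0.3 clinically important but reports power only at 0.5 and about 0.4, so the reader does not learn how the trial stands at the smallest effect in that range.

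**Working it through.** **Inputs** (Sample Size and Power Calculation; α and test confirmed in Statistical Analysis Plan): SD 1.0, so d equals the raw difference; two-sided α = 0.05; two-sample t test; 1:1 allocation; n = 150 per arm.

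**Step 1: reproduce the plan's base figure.** Normal approximation: n per arm = 2(1.960 + 0.842)²/d² = 15.70/d².

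- d = 0.5: 15.70/0.25 = 62.8, so 63 per arm (63.8 with the noncentral t). The plan's figure of about 63 reproduces, so the method matches the plan's.

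**Step 2: power at 150 per arm.** The standard error of the difference is √(2/150) = 0.1155 SD. Power ≈ Φ(d/0.1155 − 1.960).

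| d | d/0.1155 − 1.960 | Power, normal | Power, noncentral t | Plan |
|---|---|---|---|---|
| 0.5 | 2.370 | 99.1% | 99.1% | >90% (true) |
| 0.4 | 1.504 | 93.4% | 93.2% | about 80% (does not reproduce) |
| 0.3 | 0.638 | 73.8% | 73.6% | not stated |

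**Step 3: what 80% power corresponds to.**

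- At d = 0.4: 15.70/0.16 = 98.1, so 99 per arm (99.1 with the noncentral t, so 100).
- At d = 0.3: 15.70/0.09 = 174.4, so 175 per arm (175.4 with the noncentral t, so 176).
- At n = 150: detectable d = 0.325 (noncentral t).

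**Step 4: could another reading give about 80% at d = 0.4?** The claim is in units of d, so the SD cannot change it.

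| Reading | Power at d = 0.4 (noncentral t) |
|---|---|
| One-sided α 0.05 | 96.5% |
| Two-sided α 0.025 | 88.7% |
| Two-sided α 0.01 | 80.8% |
| Wilcoxon, relative efficiency 0.955 | 92.1% |
| Wilcoxon, relative efficiency 0.864 | 89.4% |
| 5% loss (142.5 per arm) | 92.0% |
| 10% loss (135 per arm) | 90.6% |
| 20% loss (120 per arm) | 87.0% |
| 33% loss (100.5 per arm) | 80.6% |

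Only two of these reach about 80%. An α of 0.01 contradicts the stated 0.05. The other is a loss of 1 − 99.1/150 = 34%, and no loss rate is stated.

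**Step 5: power at 0.3 under assumed losses.** 73.6% with complete data, and 71%, 69% and 64% at 5%, 10% and 20% loss. These rates are assumptions, since the protocol gives none.

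**The case against.** The best defence is that the section mentions inflation for dropout just before the power figures, so 80% might be meant after losses. That reading needs about a third of patients to be unusable. The sentence ties the power to 150 per arm. Outcomes are collected once, straight after the consultation, with staff on hand to help, and the missing-data rule in Data Collection and Management turns on a threshold of 5%. The reading is possible but unsupported, and if it is what was meant, the rate has to be stated.

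Several other points for the plan stand:

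- The error is in the safe direction and changes no sample size, test or decision rule.
- The abstract's figure is literally true, because 93% exceeds 80%. The claim at d=0.5 and the base figure of 63 are also correct.
- The plan claims no power at 0.3, so silence there is not a second arithmetic error.

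Two stronger conclusions are tempting but unsupported. A reader might infer that the check planned at about 50% enrolment will work from a wrong reference. The text ties that check to assumptions such as variance, whose stated reference is SD 1.0, and not to the 80% figure. A reader might also infer that a null result will be misread. The plan promises a mean difference with a 95% CI, and that interval (half-width about 1.97 × 0.1155 = 0.23 at SD 1.0) decides which effects are excluded, not the planned power.

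**Conclusion.** One phrase in the sample-size section is wrong. Power at d≈0.4 with 150 per arm is about 93%, so the stated figure is about 13 points too low. The result rests only on the section's own test, α and arm size, and assumes 150 evaluable patients per arm. It stays at 87% even with an assumed 20% loss.

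A reader should not take this as a finding that the trial is too small for 0.4; it is larger than 80% power requires there. Power at 0.3 is below 80% even with complete data (about 74%). That deserves disclosure because the plan itself places 0.3 in its clinically important range, but it accompanies the correction and is not a separate error.

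**What to change.** In Sample Size and Power Calculation, replace the power sentence with one to this effect: *With 150 evaluable patients per arm, power is about 99% at d=0.5 and 93% at d=0.4; 80% power is reached at d≈0.325; at 0.3, the low end of the range considered clinically important, power is about 74% with complete data and 69% if 10% are lost.* The 10% is illustrative and should give way to the team's own assumed loss rate.

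If the 80% was meant after losses, state instead the loss rate behind it (about one third). Align the abstract with whichever version is used.

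The cost is wording only, with no change in sample size or analysis.
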